## Abstract

**Background:**

Salvage radiotherapy (SRT) for prostate cancer (PCa) recurrence after prostatectomy offers long-term biochemical control in about 50–60% of patients. SRT is commonly initiated in patients with serum PSA levels < 1 ng/mL, a threshold at which standard-of-care imaging is insensitive for detecting recurrence. As such, SRT target volumes are usually drawn in the absence of radiographically visible disease. ^68^Ga-PSMA-11 (PSMA) PET/CT molecular imaging is highly sensitive and may offer anatomic localization of PCa biochemical recurrence. However, it is unclear if incorporation of PSMA PET/CT imaging into the planning of SRT could improve its likelihood of success. The purpose of this trial is to evaluate the success rate of SRT for recurrence of PCa after prostatectomy with and without planning based on PSMA PET/CT.

**Methods:**

We will randomize 193 patients to proceed with standard SRT (control arm 1, *n* = 90) or undergo a PSMA PET/CT scan (free of charge for patients) prior to SRT planning (investigational arm 2, *n* = 103). The primary endpoint is the success rate of SRT measured as biochemical progression-free survival (BPFS) after initiation of SRT. Biochemical progression is defined by PSA ≥ 0.2 ng/mL and rising. The randomization ratio of 1:1.13 is based on the assumption that approximately 13% of subjects randomized to Arm 2 will not be treated with SRT because of PSMA-positive extra-pelvic metastases. These patients will not be included in the primary endpoint analysis but will still be followed. The choice of treating the prostate bed alone vs prostate bed and pelvic lymph nodes, with or without androgen deprivation therapy (ADT), is selected by the treating radiation oncologist. The radiation oncologist may change the radiation plan depending on the findings of the PSMA PET/CT scan. Any other imaging is allowed for SRT planning in both arms if done per routine care. Patients will be followed until either one of the following conditions occur: 5 years after the date of initiation of randomization, biochemical progression, diagnosis of metastatic disease, initiation of any additional salvage therapy, death.

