We also assume that approximately 13% of subjects randomized to Arm 2 will have extra-pelvic metastasis detected by PSMA PET/CT, and therefore are not curable by SRT directed to the pelvis [38]. Hence the primary endpoint of the trial is the success rate of SRT. If PSMA PET/CT detects distant metastases, then local salvage with SRT is not a medically indicated therapy because it is not curative. It is therefore not standard-of-care to perform SRT in patients with evidence of distant metastases. The current standard-of-care is to offer SRT to patients who have no evidence of metastatic disease. We acknowledge that patients in the trial who do not undergo PSMA PET/CT may have “hidden/unknown” metastatic disease, but these patients would still receive SRT per routine care. An intention to treat analysis would classify subject who undergo PSMA PET/CT and are found to have distant metastases as failure even without having received treatment. Therefore, the primary endpoint of the trial is the success rate of SRT in patients who actually receive SRT. The question the trial asks is: “*Within patients for whom SRT is appropriate given the imaging results, is the rate of SRT success different between standard-of-care imaging and PSMA PET/CT arms?*”. As such, it would be inappropriate for patients who do not undergo SRT to be included for the primary endpoint. Therefore, patients with PSMA PET/CT showing distant metastases will not be included for the primary endpoint analysis but will still be followed. Based on these estimates, 193 subjects are required to be randomized in a 1:1.13 ratio (90 in control group and 103 in the PSMA group). Randomized, eligible, sample size in each group is therefore *n* = 90.

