### Outcome measures

#### Primary endpoint measure

Success rate of SRT measured as rate of biochemical progression-free survival (BPFS) after initiation of SRT (Time Frame: From date of initiation of SRT until the date of first documented progression or death from any cause, whichever comes first, assessed up to 5 years). Biochemical progression is defined as a serum PSA ≥ 0.2 ng/mL and rising after completion of SRT (second confirmatory value must be rising and separated by ≥ 1 month).

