#### Secondary endpoints measures

5-year BPFS rate from date of randomization (Time Frame: 5 years)Metastasis free-survival from date of randomization (Time Frame: 5 years). Diagnosis of extra-pelvic metastatic (M1) disease can be obtained by any imaging or biopsy.Initiation of additional salvage therapy after completion of SRT measured as rate of additional PCa therapy initiation-free survival (Time Frame: 5 years; from the initiation of SRT until the first documented initiation of any additional PCa treatment).Change in initial treatment intent.

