#### Study duration

We expect to enroll the 193 patients within 2 years of study initiation. Patients will be followed by UCLA Nuclear medicine (phone calls/ secure emails) until either one of the following conditions occur:5 years after the date of initiation of randomization.Biochemical progression.Diagnostic of extra-pelvic metastatic disease by any imaging or biopsy.Initiation of any additional salvage therapy.Death.

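### Study follow-up ends at biochemical progression, so metastases, new therapy and deaths after it go unrecorded for the 5-year secondary endpoints, and the M1 stop contradicts the promise to keep following scan-positive Arm 2 patients

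*Protocol article*

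**What the plan says.** **When follow-up ends.** The abstract (Methods) states: "Patients will be followed until either one of the following conditions occur: 5 years after the date of initiation of randomization, biochemical progression". The list there goes on to name M1 disease, further salvage therapy and death. The Study duration section applies the same list to the study team's calls and emails. After 5 years and biochemical progression, its remaining items are: "Diagnostic of extra-pelvic metastatic disease by any imaging or biopsy.Initiation of any additional salvage therapy.Death".

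**How data are collected.** Under Follow-up, the study team telephones patients every 3 to 4 months in year 1 and every 6 months afterwards. Each call asks for the latest PSA, any new salvage therapy and any imaging that suggests progression. The same section says imaging is usually prompted by suspected recurrence.

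**What must be measured.**
- Primary endpoint: biochemical progression-free survival (BPFS) from the start of salvage radiotherapy (SRT), "until the date of first documented progression or death from any cause, whichever comes first, assessed up to 5 years". Biochemical progression is defined by PSA alone, with a confirmatory value at least a month later.
- Secondary endpoints: 5-year BPFS from randomization; "Metastasis free-survival from date of randomization (Time Frame: 5 years"); and freedom from additional therapy over 5 years, running "from the initiation of SRT until the first documented initiation of any additional PCa treatment".

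**Arm 2 patients with distant metastases on the scan.** The rationale section says they "will not be included for the primary endpoint analysis but will still be followed". The abstract says the same.

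**The concern.** The list stops contact at whichever event comes first, but the endpoints end at different events. A stop that completes one endpoint cuts another short.

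Biochemical progression matters most. It completes BPFS, but it comes just when metastasis is likely to be looked for and further therapy considered. Patients who progress are at higher risk of both, so censoring them at that moment is informative. The trial also expects more progression in the control arm, so the censoring is unequal between arms. An analysis plan cannot repair this, because the later data are never collected.

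The metastasis stop raises a second problem. An extra-pelvic lesion on the study scan is an M1 diagnosis by imaging, so the list would end contact at the scan. The rationale section and the abstract promise the opposite for the same patients. They are already outside the primary analysis, which makes BPFS from randomization the natural check on the whole randomized population.

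**Working it through.** **1. Reproduce the plan's figures** (Sample size determination).
- Rates from −ln(S)/5: control −ln(0.60)/5 = 0.1022; PSMA −ln(0.80)/5 = 0.0446; dropout −ln(0.90)/5 = 0.0211. All match. The hazard ratio is 0.0446/0.1022 = 0.436.
- Schoenfeld events at two-sided 0.05 and 80% power: 4 × (1.96 + 0.8416)² / (ln 0.436)² = 45.6, rounded up to 46.
- An exponential test with 90 per arm, 5 years and this dropout has about 80% power.

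The sample size stands, and nothing below changes it.

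**2. Which stop completes which endpoint**

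| Stop | BPFS | Metastasis-free survival | Freedom from additional therapy |
|---|---|---|---|
| Biochemical progression | complete | cut short | cut short |
| M1 | handling not stated | complete | cut short |
| New salvage therapy | handling not stated | cut short | complete |

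**3. How many leave at progression.** With hazard h and dropout d, P(failure observed within 5 years) = h/(h+d) × [1 − exp(−5(h+d))].
- Control: 0.1022/0.1233 × [1 − exp(−0.6165)] = 0.381; × 90 = 34.3.
- Arm 2: 0.0446/0.0657 × [1 − exp(−0.3285)] = 0.190; × 90 = 17.1.

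The ratio is 34.3/17.1 = 2.0. Ignoring dropout, the counts are 0.40 × 90 = 36 and 0.20 × 90 = 18. The planned failure rate covers progression or death, so any deaths among these patients reduce the number who leave at progression.

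Mean follow-up under the list is [1 − exp(−5(h+d))]/(h+d) = 3.73 years (control) and 4.26 years (Arm 2). If only dropout ended it early, it would be [1 − exp(−5 × 0.0211)]/0.0211 = 4.75 years in both arms.

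**4. What this could do to metastasis-free survival (illustration only).** The document gives no M1 hazard. Assume 0.002 to 0.01 per year before progression and 0.05 to 0.20 per year after it, equal in both arms, with no dropout. Then 56–95% of control and 35–89% of Arm 2 metastases within 5 years fall after follow-up has ended.

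One case, with 0.01 before and 0.10 after: the 5-year M1 risk is 12.9% (control) and 8.7% (Arm 2), but only 3.8% and 4.4% would be recorded. An analysis censored at progression estimates just the pre-progression hazard, giving 1 − exp(−5 × 0.01) = 4.9% in each arm. A real difference would disappear. Other assumed hazards give other results.

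**5. Scan-positive Arm 2 patients.** 0.13 × 103 = 13.4, about 13 patients.
- Metastasis-free survival: M1 on any imaging counts, so they are events at the scan and are not lost.
- Freedom from additional therapy: it starts at SRT, so those who never start SRT are not in it.
- BPFS from randomization: read literally, the stop leaves them with no PSA data after the scan, in one arm only.

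**The case against.** A reader might infer three stronger claims. The documents do not support them.

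- **That the two secondary endpoints cannot be observed at all.** M1, new therapy or death as the first event is recorded. Confirmation of progression needs a second PSA at least a month later, imaging can start on suspicion, and each call asks about PSA, therapy and imaging together. Some metastases and therapy starts close to progression would therefore be captured. Later ones would not.
- **That the scan-positive Arm 2 patients are lost at the scan.** The abstract and rationale say they will be followed, and a specific statement may be taken to override a general list. This is a contradiction to reconcile, not a settled loss.
- **That the primary endpoint is informatively censored.** Stopping at biochemical progression is the primary event, so it censors nothing. The question arises only for M1 or new therapy before confirmed PSA progression. The article does not say that such patients are censored, its wording on first documented progression could be read to include M1, and an analysis plan may settle it. The number affected is unknown.

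It can also fairly be said that 34 and 17 count biochemical progressions, not lost metastases. That stands: they measure who leaves observation, not what is missed.

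Finally, the Data collection section and the Discussion mention following enrolled patients for 5 years. Both do so for the case of under-enrolment, and neither withdraws the stopping list.

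**Conclusion.** The point holds as a conflict within the protocol's own text. The stopping list does not fit 5-year metastasis-free survival or freedom from additional therapy, because events after biochemical progression fall outside follow-up. About 34 of 90 control and 17 of 90 Arm 2 patients would leave this way. That assumes the planning rates hold, that hazards are constant, and that the failures are progressions rather than deaths. The censoring is informative and about 2:1 between arms. The number of metastases or therapy starts lost cannot be derived from the document, and the illustrated range rests on assumed hazards.

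Separately, the M1 stop contradicts the promise to follow about 13 of 103 Arm 2 patients. What is at risk there is BPFS from randomization.

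How M1 or new therapy before confirmed PSA progression enters the primary analysis is a lesser point of clarification. The planned 46 events and 80% power are unaffected.

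**What to change.** 1. End study follow-up only at 5 years, death or withdrawal. Continue the existing 6-monthly calls after biochemical progression, M1 or new therapy for every randomized patient, including those who never start SRT.
2. Reconcile the stopping lists in the abstract and Study duration with the statements in the abstract and rationale that scan-positive Arm 2 patients will still be followed.
3. As a secondary point, state whether M1 or new therapy before confirmed PSA progression is an event or is censored in the primary analysis, and run the alternative as a sensitivity analysis. Making the start of salvage therapy a primary event is not required. In an open-label trial it would turn clinicians' timing decisions into events, so that choice should be argued on its merits.

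The cost is a wording change and more calls to patients who have progressed. No new procedure is needed, and the sample size does not change.

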**Discussion:**

This is the first randomized phase 3 prospective trial designed to determine whether PSMA PET/CT molecular imaging can improve outcomes in patients with PCa early BCR following radical prostatectomy.

**Acronym:**

PSMA-SRT Phase 3 trial.

**Clinical trial registration:**

■ IND#130649◦ Submission: 04.26.2016◦ Safe-to-proceed letter issued by FDA: 05.25.2016■ UCLA IRB #18–000484,■ First submission: 3.27.2018■ Date of approval: 5.31.2018■ UCLA JCCC Short Title NUC MED 18–000484■ NCI Trial Identifier NCI-2018-01518■ ClinicalTrials.gov Identifier NCT03582774■ First Submitted: 06.19.2018■ First Submitted that Met QC Criteria: 06.27.2018■ First Posted: 07.11.2018■ Last Update Submitted that Met QC Criteria: 07.17.2018■ Last Update Posted: 07.19.2018

**Trial status:**

Current Trial Status Active as of 08/13/2018

Trial Start Date 09/01/2018-Actual

Primary Completion Date 09/01/2023-Anticipated

Trial Completion Date 09/01/2024-Anticipated

## Introduction

### Background

Prostate cancer (PCa) is expected to have an incidence of 161,000 and a mortality of 27,000 in the US in 2017 [1]. Curative treatments for localized PCa include radical prostatectomy or radiotherapy [2]. After failure of local therapy, recurrence is detected by rising serum PSA levels. Biochemical recurrence (BCR) occurs in 20 to 80% of patients within 10 years after radical prostatectomy, with the risk of failure dependent on NCCN risk group, pathologic features, and genomic classification [3, 4]. Locally recurrent disease after radical prostatectomy may be cured by salvage radiation therapy (SRT) [5]. Overall, SRT offers long-term biochemical control in about 50–60% of patients [6, 7], depending on pre-SRT prostate-specific antigen (PSA) [5], RT dose [8] and risk group [9]. Results from RTOG 0534 trial [10], which compared three salvage RT regimens: SRT directed to the prostate bed alone, SRT directed to the prostate bed with 4–6 months of concurrent ADT, and SRT directed to the prostate bed and nodes with 4–6 months of concurrent ADT, was recently presented [11]. Five-year biochemical recurrence free survivals were higher than expected in all arms at 71.1, 82.7, and 89.1%, respectively. Pre-SRT PSA levels were < 1.0 ng/mL in 90% of patients and only 17% of patients enrolled had a pathologic Gleason Score of 8 or higher. It is likely that these findings will impact routine practice [11]. For high-risk patients, however, 5-year BCR after SRT reaches 70% [6, 12, 13].

Intuitively, SRT is only curative if recurrent disease is completely encompassed by the irradiated volumes. Therefore, accurate localization of recurrent disease is critical. However, standard-of-care imaging modalities are too insensitive to identify recurrence sites in time to guide salvage treatment [14–16]. In practice, SRT is commonly initiated in patients with serum PSA levels < 1 ng/mL, a threshold at which standard-of-care imaging is insensitive for detecting recurrence [15]. As such, SRT target volumes are usually delineated in the absence of radiographically visible disease (gross disease). Based on an expert consensus panel the RTOG (Radiation Therapy Oncology Group) published contouring guidelines for both prostate bed and pelvic lymph node (LN) Clinical Target Volumes (CTV) as these regions often harbor occult tumors not seen on standard-of-care imaging [17, 18]. These consensus CTV are applied in ongoing trials and guide routine clinical care.

The effectiveness of any local therapy depends on accurate imaging to rule out areas of disease that would remain untreated. The lack of sensitivity of standard-of-care imaging for recurrent PCa combined with a sensitive and specific biomarker of early disease recurrence (serum PSA level) generates a unique challenge for local treatment of PCa BCR: cancer is present, but we do not know where it is. There is thus an unmet clinical need to improve target delineation in patients with potentially curable PCa with early BCR.

^68^Ga-PSMA-11 (PSMA) PET/CT is superior to standard-of-care imaging for detecting regional and distant metastatic recurrent PCa at low PSA levels [19–22], highly specific [22] and reproducible [23]. Detection rates of about 50% are reported even at PSA levels of < 0.5 ng/ml [21, 22] and greater than 95% when PSA > 2 ng/mL [24, 21]. PSMA PET/CT outperformed planar bone scan for detection of osseous metastases in large retrospective analyses [25, 26]. The detection rate of PSMA PET/CT for recurrent PCa exceeds that of choline PET/CT [27, 28], and may exceed that of ^18^F-Fluciclovine PET/CT [29].

Therefore PSMA PET/CT has the potential to guide and improve SRT planning in numerous ways [30]. First, PSMA PET/CT defined gross disease within a target volume can be prescribed a higher dose. Second, CTVs can be expanded to encompass areas of disease not seen by current first-line imaging and not normally targeted by consensus CTVs. Third, evidence of metastatic disease indicates that local therapy alone would not offer cure, SRT may be considered futile and abandoned. The potential impact of PSMA PET/CT on SRT planning has been assessed in several studies (Table 1) [30–43]. Taken as a group, the pooled median rate of impact of PSMA PET/CT on SRT planning is 50% (range 17–87%). Our recent multicenter post-hoc analysis of 270 patients with early BCR after prostatectomy showed that PSMA PET/CT would have had a major impact in 19% of patients [38]. Importantly, a major impact was defined as PSMA-positive disease outside planning target volumes expanded from CTVs covering both the prostate bed and pelvic lymph nodes up to L4/L5, which is more expansive than the volumes used in RTOG 0534 [10, 38]. Overall, the addition of PSMA PET/CT would have had an impact on SRT planning in half of patients with a PSA < 1 ng/mL even when using the most generous target volumes. This is the most relevant patient cohort to assess the impact of PSMA PET/CT on SRT.

**Table 1 Tab1:** Studies That Assessed Impact of PSMA PET/CT on SRT Planning

Author	Year	*n*	PSA (ng/ml) Median (range)	PSMA+	Extrapelvic PSMA+	Any SRT Planning Change	SRT Considered Futile
Shakespeare	2015	18	1.1 (0.017–20.4)	NA	NA	46%	NA
van Leeuwen	2015	70	0.2 (0.05–0.99)	55%	6%	35%	7%
Sterzing	2016	42	2.8 (0.16–113)	60%	NA	61%	NA
Bluemel	2016	45	0.67 (0.10–11.2)	54%	9%	42%	4%
Albisinni	2016	48	2.2 (0.72–6.7)	NA	NA	76%	NA
Schiller	2017	31	0.71 (0.12–14.7)	100%	3%	87%	0%
Henkenberens	2017	39	1.2 (0.3–15.5)	85%	46%	59%	13%
Schmidt-Hegemann	2017	49	0.49 (0.15–6.24)	NA	4%	57%	NA
Habl	2017	83	0.69 (0.09–14.7)	71%	10%	57%	0%
De Bari	2018	12	0.51 (0.10–1.62)	NA	NA	17%	8%
Koerber	2018	71	1.2 (0.03–41.24)	NA	51%	54%	3%
Frenzel	2018	75	0.2 (0.02–653.2)	NA	NA	43%	NA
Farolfi	2018	119	0.32 (0.20–0.50)	35%	21%	30%	18%
Calais	2018	270	0.48 (0.03–1.0)	49%	13%	19%	12%

Few retrospective studies with short-term follow-up reported patient outcome after PSMA PET/CT-based SRT for PCa post-prostatectomy recurrence (Table 2) [44–48]. The mean response rate from these studies is 74% (range 60–83%) after a mean follow-up time of 19 months (range 10.5–29). Interestingly Emmet et al. reported in 99 patients with BCR and PSA 0.05 to 1.0 ng/mL that PSMA PET was independently predictive of treatment response to SRT and stratified men with good response to SRT (negative PSMA (85%) or fossa-confined PSMA (81%)) versus men with poor response to SRT (PSMA N1 (61%) or PSMA M1 (30%)) after a median follow-up of 10.5 months [46].

**Table 2 Tab2:** Studies That Assessed Outcome of PSMA PET/CT-based SRT

Author	Year	*n*	Response rate	Median follow-up (months)
Henkenberens	2017	23	79%	12.4
Zschaeck	2017	20	60%	29
Emmett	2017	99	72%	10.5
Schmidt-Hegemann	2018	129	83%	20
Schmidt-Hegemann	2018	90	78%	23

However, it remains unclear if incorporation of PSMA PET/CT imaging into the planning of SRT could improve its likelihood of success. There is no randomized prospective trial designed to determine whether PSMA PET/CT can improve outcome at 5 years in patients with PCa early BCR following radical prostatectomy**.** The purpose of this trial is to evaluate the success rate of SRT for recurrence of PCa after prostatectomy with and without planning based on PSMA PET/CT.

### Rationale for study design and hypothesis

The overall study design is shown in Fig. 1.

**Fig. 1 Fig1:**
[figure not shown]
Study Design. 68Ga-: Gallium-68; ADT: Androgen deprivation therapy; PET/CT: Positron Emission tomography/Computed Tomography; PSA: Prostate-specific antigen; PSMA: Prostate-specific membrane antigen; SRT: Salvage Radiation Therapy; SBRT: Stereotactic Body Radiation Therapy; UCLA: University of California, Los Angeles

In our recent multicenter post-hoc analysis of 270 patients with early BCR (PSA < 1.0 ng/ml) after prostatectomy we found that 52/270 patients (19%) had at least one lesion detected by PSMA PET/CT which was not covered by the standard radiation fields that covered both the prostate bed and pelvic lymph nodes (RTOG consensus delineations with superior extent extended to L4/L5): extra-pelvic disease was seen in 13% of patients and out-of-field pelvic disease was seen in 7% of patients [38]. SRT delivered based on these volumes would not have generated a durable PSA response. PSMA PET/CT imaging can improve patient selection for successful SRT by excluding patients with M1 disease where SRT would not be curative (13%) and by improving the coverage of the recurrent lesions by the pelvic radiation fields (7%). Therefore, we hypothesized that the incorporation of PSMA PET/CT to SRT planning will improve 5-year PFS by 20%. Based on available published literature [5–9, 12] we assume 5-year PFS to be 60% in Arm 1 (standard SRT) and 80% in Arm 2 (PSMA PET/CT based SRT).

We also assume that approximately 13% of subjects randomized to Arm 2 will have extra-pelvic metastasis detected by PSMA PET/CT, and therefore are not curable by SRT directed to the pelvis [38]. Hence the primary endpoint of the trial is the success rate of SRT. If PSMA PET/CT detects distant metastases, then local salvage with SRT is not a medically indicated therapy because it is not curative. It is therefore not standard-of-care to perform SRT in patients with evidence of distant metastases. The current standard-of-care is to offer SRT to patients who have no evidence of metastatic disease. We acknowledge that patients in the trial who do not undergo PSMA PET/CT may have “hidden/unknown” metastatic disease, but these patients would still receive SRT per routine care. An intention to treat analysis would classify subject who undergo PSMA PET/CT and are found to have distant metastases as failure even without having received treatment. Therefore, the primary endpoint of the trial is the success rate of SRT in patients who actually receive SRT. The question the trial asks is: “*Within patients for whom SRT is appropriate given the imaging results, is the rate of SRT success different between standard-of-care imaging and PSMA PET/CT arms?*”. As such, it would be inappropriate for patients who do not undergo SRT to be included for the primary endpoint. Therefore, patients with PSMA PET/CT showing distant metastases will not be included for the primary endpoint analysis but will still be followed. Based on these estimates, 193 subjects are required to be randomized in a 1:1.13 ratio (90 in control group and 103 in the PSMA group). Randomized, eligible, sample size in each group is therefore *n* = 90.

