### Sample size determination

In our a previous study [38], 52/270 patients (19%) had at least one lesion detected by PSMA PET/CT which was not covered by the standard radiation field that covered both the prostate bed and pelvic lymph nodes (RTOG consensus delineations). Standard SRT would not have resulted in durable disease control because gross disease would have been missed. Therefore, we hypothesized that the incorporation of PSMA PET/CT to SRT planning will improve 5-year PFS survival by 20%. Based on available published literature we estimated the 5 y PFS at 60% with standard SRT [5–9, 12]. Therefore, we assume 5-year PFS to be 60% in Arm 1 (standard SRT) and 80% in Arm 2 (PSMA PET/CT based SRT). We also assume that approximately 13% of subjects randomized to Arm 2 will have extra-pelvic metastasis detected by PSMA PET/CT, and therefore are not curable by SRT directed to the pelvis [38]. Based on these estimates, 193 subjects are required to be randomized in a 1:1.13 ratio (90 in control group and 103 in the PSMA group). Randomized, eligible, sample size in each group is therefore *n* = 90. When the randomized, eligible, sample size in each group is 90, with an estimated total number of events required of 46, an exponential maximum likelihood test of equality of survival curves with a 0.050 two-sided significance level will have 80% power to detect the difference between a PSMA group exponential parameter of 0.0446 (assuming a 5 year failure rate of 20%) and a control group exponential parameter of 0.1022 (assuming a 5-year failure rate of 40%), which equals a constant hazard ratio of 0.436; this assumes a maximum follow-up time of 5 years and a common exponential dropout rate of 0.0211 (assuming 10% 5-year drop-out rate in each group). The planned log-rank test should have similar power to the exponential MLE survival test.

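### The 80% rate assumed for Arm 2 does not follow from the 13% and 7% it is built on: the excluded 13% do not become successes, the stated mechanisms give about 77%, and power there is about 67-69%

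*Protocol article*

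**What the plan says.** In the protocol article, the section on the rationale for study design and hypothesis reports from a previous series of 270 patients that 52 (19%) had a lesion outside standard fields: "extra-pelvic disease was seen in 13% of patients and out-of-field pelvic disease was seen in 7% of patients". It says standard SRT would not have controlled these patients durably. It then names two routes to improvement, excluding M1 patients (13%) and better pelvic coverage (7%), and concludes that 5-year PFS will therefore rise by 20%: "we assume 5-year PFS to be 60% in Arm 1 (standard SRT) and 80% in Arm 2 (PSMA PET/CT based SRT".

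The sample size section reaches the same 20% from the 19% total and repeats: "Therefore, we assume 5-year PFS to be 60% in Arm 1 (standard SRT) and 80% in Arm 2 (PSMA PET/CT based SRT". The cited literature is tied there to the 60% figure. The resulting design has 90 analysed per arm, a "0.050 two-sided significance level will have 80% power" and 46 events, "which equals a constant hazard ratio of 0.436".

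The rationale also says that "patients with PSMA PET/CT showing distant metastases will not be included for the primary endpoint analysis but will still be followed". The abstract, the section on SRT management and the statistical methods section repeat this exclusion. It is the reason Arm 2 is enlarged from 90 to 103.

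**The concern.** The same 13% is used twice. It supplies 13 of the 20 points of expected gain, and it is also the group taken out of the Arm 2 analysis set. Removing expected failures from a denominator raises the success rate, but not by one point for each percent removed, and it creates no successes. Adding 13 and 7 to 60 is valid only if all 100 patients stay in the denominator and all 20 become successes.

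The hazard ratio, the 46 events, the 80% power and the 193 patients all rest on the 80%. In addition, part of the expected difference would appear even if no patient gained disease control, and the sample size text does not say how much.

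**Working it through.** **Inputs (sample size section).** 5-year PFS 60% and 80%; hazards 0.1022 and 0.0446 per year; dropout hazard 0.0211; 90 per arm; 5 years of follow-up, taken here as 5 years for each patient; two-sided 0.05. From the rationale: 13%, 7%, 19%.

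**Formulas.**
- Hazard λ = -ln(S)/5.
- Expected events per arm = 90 × λ/(λ + d) × [1 - exp(-5(λ + d))], with d = 0.0211.
- Schoenfeld events for 80% power = 4 × (1.960 + 0.842)² / (ln HR)².
- Schoenfeld power = Φ(|ln HR| × √E / 2 - 1.960), with E the expected events.
- Exponential test on the hazard difference Δ: power = Φ[(Δ - 1.960√V0)/√V1]. V1 is the sum of λ²/E over the arms; V0 is the same with the average hazard in both arms.

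**Plan's own case, 60% versus 80%.**
- HR = 0.0446/0.1022 = 0.436 (0.437 unrounded).
- Events needed = 31.4/0.686 = 45.8, so 46, as stated.
- Expected events = 34.3 + 17.1 = 51.4.
- Exponential test: Δ = 0.0575, √V0 = 0.0202, √V1 = 0.0205, power 80.8%.
- Schoenfeld power 84.4%; simulated log-rank (8,000 runs) 82.8%.

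The stated 46 events and 80% power are reproduced.

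**Arm 2 rate from the stated mechanisms, per 100 patients.**
- Control: 60 successes and 40 failures. On the plan's premise the failures include the 13 and the 7.
- Exclusion alone: 60/(100 - 13) = 60/87 = 69.0%, a gain of 9.0 points.
- Exclusion plus all 7 rescued: 67/87 = 77.0%, a gain of 17.0 points.
- With the 19% total, 19 - 13 = 6 rescued: 66/87 = 75.9%.
- To reach 80%: 0.80 × 87 = 69.6 successes, so 9.6 rescued per 100 rather than 7.

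**Power at the derived rates, same design.** At 77.0%:
- HR = ln(0.770)/ln(0.60) = 0.511.
- Events needed = 31.4/0.450 = 69.8, so 70, against 34.3 + 19.7 = 54.0 expected.
- Exponential test: Δ = 0.0499, √V0 = 0.0208, √V1 = 0.0210, power 66.7%.
- Schoenfeld: Φ(0.671 × √54.0 / 2 - 1.960) = Φ(0.50) = 69.3%.

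| Arm 2 5-year PFS | HR | Events needed (Schoenfeld) | Events expected | Exponential test | Schoenfeld | Simulated log-rank |
|---|---|---|---|---|---|---|
| 80% (plan) | 0.437 | 46 | 51.4 | 80.8% | 84.4% | 82.8% |
| 77.0% (7 rescued) | 0.511 | 70 | 54.0 | 66.7% | 69.3% | 68.5% |
| 75.9% (6 rescued) | 0.541 | 84 | 55.0 | 60.4% | 62.5% | 60.6% |

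**Sensitivity to the number rescued.** Eight per 100 gives 68/87 = 78.2% and power of about 72-76%; nine gives 79.3% and 77-81%; ten gives 80.5% and 82-86%.

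**The case against.** The strongest reply is that 77% is not an upper limit.

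- The 7% was measured against fields covering the prostate bed and the pelvic nodes up to L4/L5, which the background section describes as wider than those of an earlier trial. This trial also allows prostate-bed-only SRT at the physician's discretion, and a PSMA-positive pelvic node lies outside such a field. The share of correctable misses could therefore exceed 7%.
- The background section lists a higher dose to visible disease as a benefit, and the section on SRT management permits focal dose escalation.
- Fewer than three further rescues per 100 would restore 80%.

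This stands. A reader might infer that 80% is unattainable, or that the trial cannot have its stated power. The documents support neither. What they show is that the two mechanisms with figures do not yield 80%. The others have no figure, and the rationale does not count them in its 20 points.

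A reader might also infer that the power calculation is wrong. It is not: it is correct for its inputs, and the rates are worded as assumptions. The weakness lies in how the 80% was derived.

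Finally, the exclusion is disclosed, its reason is given, and hidden metastases in controls are acknowledged. That is fair. But the size of its contribution to the expected difference is nowhere stated.

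The response rates in Table 2 (60-83%) do not rescue the 80%. Their median follow-up is 10.5 to 29 months, and the protocol does not cite them as its basis.

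**Conclusion.** The point holds as a fault in the derivation of the planning effect. The quantified mechanisms give about 77% in the SRT-treated set (about 76% with the 19% total), not 80%. About 9 of the 17 points come from exclusion alone. If the true rate were 77%, the chance of missing the effect would be about one third rather than about one fifth.

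This rests on the plan's own premises: 60% in control, the 13% and 7% all failing under standard SRT, the 7% all rescued in Arm 2, and nobody else's outcome changing. The third premise is favourable; if the 7 succeed only at the 75% rate of the other 80 patients (60/80), Arm 2 is (60 + 5.25)/87 = 75.0% and power about 55-57%. The last premise may be unfavourable, for the reasons given in the objection. It also assumes 5 years of follow-up for each patient and exponential survival, as the plan does.

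**What to change.** Correct the derivation in the rationale and in the sample size section, in one of two ways:

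1. Use about 77% for Arm 2 and restate the hazard ratio (about 0.51) and the power with 90 per arm (about 67-69%).
2. Keep 80%, but only with an explicit, quantified further basis that accounts for about 9.6 rather than 7 rescued per 100 (for example, pelvic nodes missed by bed-only fields, or focal dose escalation), and report the 67-69% power at 77% beside it.

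In either case, state that exclusion alone is expected to move Arm 2 from 60% to about 69%, so that a positive result can be read against that figure.

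The cost is a change of wording and a less favourable stated power. Enrolment, the test and trial conduct are unchanged.
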